### 2.3. Treatment groups

A standardized program of balance exercises and VFBT will be provided to participants across groups twice a week for six weeks, totaling twelve sessions. VFBT is a task-specific training approach in which participants receive real-time visual feedback on their balance performance during static and dynamic standing tasks [37,38,47]. Each training session will last approximately 90 minutes, including a warm-up period with light aerobic activity (e.g., marching in place), lower-limb stretching, and low-intensity controlled weight shifting exercises customized to each participant’s functional level, followed by 60 minutes of active training. The conceptual framework of our setup, which includes VFBT with FES & TSS, is depicted in Fig 2. For VFBT, participants will stand in front of a monitor while a Wii-Balance Board (Nintendo, Japan) records center of pressure (COP) displacement, which is displayed on the screen as a cursor to guide postural adjustments. Training includes interactive games such as target tracking, ellipse tracing, color-matching, and hunting [37,38,47]. Participants will be encouraged not to use assistive devices except when necessary for safety in the event of difficulty with independent standing. A ceiling-mounted harness will be provided to each participant to prevent falls while allowing movements during the training.

**Fig 2 pone.0346491.g002:**
[figure not shown]
Visual feedback balance training set up with functional electrical stimulation (FES) and transcutaneous spinal stimulation (TSS).

#### 2.3.1. Group 1: VFBT with Sham FES + Sham TSS.

Participants in this group will receive the sham simulation during VFBT. One electrode (5 × 10 cm) will be positioned over the thoracolumbar spine between T10-L2, and two inter-connected reference electrodes (5 × 5 cm) will be placed over the abdomen, medial to the anterior superior iliac spine. For FES, surface electrodes will be placed over the dorsi-flexors (5 × 5 cm) and the plantar-flexors (5 × 10 cm) on both sides. During the first 30 seconds of each session, there will be brief sensory-level stimulation, which will be dropped to 0 mA.

#### 2.3.2. Group 2: VFBT with Active FES + Sham TSS.

Participants in this group will receive active FES for ankle muscles and sham TSS during VFBT. At the start of each session, motor threshold and maximum tolerable stimulation intensities will be determined for each muscle. FES will be delivered at a frequency of 30 Hz with a pulse width of 0.3 ms (MyndSearch, MyndTec Inc., Mississauga, ON, Canada). The closed-loop FES activates ankle muscles in response to real-time feedback from the Wii-Balance Board, which monitors the user’s COP. The filtered COP represents the body’s center of mass (COM). The body’s COM is continually monitored and the level of stimulation adjusted accordingly on a moment-to-moment basis, mimicking intact postural control. Stimulation intensity will vary between the motor threshold and 90% of the maximal tolerable intensity to facilitate the intended movements during balance tasks [37,38,47]. Sham TSS will be administered via a brief sensory-level ramp, then decreased to 0 mA, similar to group 1.

#### 2.3.3. Group 3: VFBT with Active FES +Active TSS.

Participants in this group will receive the same active FES protocol described above, plus active TSS which will be applied using surface electrodes positioned over the T10–L2, with anterior electrodes placed over the abdomen medial to the anterior superior iliac spine (Fig 2). Stimulation will be delivered continuously at a sub-motor threshold at 30 Hz using biphasic, 1 ms pulse width (Stim2Go, Pajunk® GmbH, Germany) during VFBT.

### 2.4. Treatment outcomes

The study outcomes have been categorized into feasibility, acceptability, safety, efficacy, and neurophysiological outcomes quantifying neuroplasticity. Below is a full explanation of each outcome category.

#### 2.4.1. Feasibility outcomes.

Feasibility outcomes will include recruitment rate, retention rate, and adherence [48]. Recruitment rate refers to the percentage of eligible participants who enrolled relative to the number screened. Retention is defined as the proportion of participants who completed all three assessment time points, and adherence is measured by how many of the 12 training sessions each participant completed.

#### 2.4.2. Acceptability outcomes.

The Technology Acceptance Model 2 (TAM-2) questionnaire will be used immediately after training to capture patients’ perspectives of perceived usefulness of the technology for training [49,50]. TAM-2 includes questions reflecting different domains of technology acceptance, including behavioral intention (e.g., intention to use again, social influence), perceived ease of use (e.g., enjoyment, comfort/safety), perceived usefulness (e.g., goal attainment, impact on daily life), and usage behavior (e.g., real-world integration, user preferences, individualization) [49]. Participants will also take part in semi-structured qualitative interviews guided by a previously developed framework based on TAM-2 [49]. The guide consists of open-ended questions and encourages participants to share their thoughts and experience regarding perceived benefits of the training program across different domains aligned with the TAM-2 framework (behavioral intention, perceived ease of use, usefulness, and usage behavior) [49].

#### 2.4.3. Safety outcomes.

All adverse events will be recorded and reported throughout the study period. Adverse events may include skin irritation, muscle soreness, discomfort, fatigue, dizziness, risk of loss of balance, or any unexpected pain. If participants request to withdraw from the trial, the intervention will be discontinued, and they will be withdrawn from the trial without penalty or impact on their usual medical care. All adverse events and the actions taken to address them will be reported to the Review Ethics Board. Participants will receive medical treatment at no cost to them in accordance with institutional policies in the event of an adverse event.

#### 2.4.4. Efficacy outcomes (Exploratory).

The clinical performance-based tests, biomechanical balance tests, and patient-reported outcomes will be examined at baseline, immediately post-training, and at 8 weeks post-training. Performance-based tests will include the BBS, Timed Up and Go (single- and dual-task), and the Timed 25-Foot Walk (T25FW). The BBS is a 14-item performance-based measure of functional balance that has demonstrated excellent reliability and validity in PwMS [51,52]. The TUG assesses functional mobility and dynamic balance and has demonstrated good reliability and sensitivity to change in MS, including under dual-task conditions [51,52]. The T25FW is a commonly used measure of walking speed that has shown to be reliable and valid in PwMS [51,52]. We will additionally test static and dynamic balance performance using a force plate to measure sway characteristics and limits of stability.

Patient-reported outcomes will include MS Walking Scale-12 (self-reported measure of walking abilities and limitations), Falls Efficacy Scale–International (concern about falling during daily activities), and the Activities-specific Balance Confidence Scale (balance confidence during daily activities). All of these patient-reported outcomes have demonstrated good reliability and validity in PwMS [53–56]. A global rating of change scale will be used to measure participants’ overall improvement immediately and at 8 weeks post-training compared to the baseline. The scale consists of a 7-point Likert scale ranging from very much worse to very much improved [57,58].

#### 2.4.5. Biomechanical balance measures.

Participants will be asked to stand quietly on a force plate for 100 seconds under two conditions: eyes open, and COP displacements will be recorded. For the dynamic balance test, they have to lean as far as possible in eight different directions without losing balance and maximal COP excursion will be quantified.

#### 2.4.6. Neurophysiological outcomes.

To measure corticospinal excitability of the leg muscles, motor evoked potentials (MEPs) will be measured using TMS with a double-cone coil (MEGA TMS system, Soterix Medical Inc., USA). Fig 3 shows the testing position for measuring MEPs. Electromyography (EMG) electrodes (Kendall TM Medi-Trace ® Mini 130 Foam Electrodes, Neurotronics, NSW, Australia) will be placed over the soleus and tibialis muscles on the more affected side. In case of symmetrical lower-limb involvement, defined as no difference in single-leg stance time between the two sides on the BBS, we will record from the dominant side. EMG signals will be amplified (×500) and band-pass filtered from 10 Hz to 1 kHz (Bortec Biomedical, AB, Canada).

**Fig 3 pone.0346491.g003:**
[figure not shown]
Measurement of corticospinal and spinal excitability. Motor evoked potentials (MEPs) are evoked by transcranial magnetic stimulation (TMS), and spinal motor evoked potentials (SMEPs) are evoked by transcutaneous spinal stimulation (TSS).

The coil will be placed over the primary motor cortex, and the hotspots will be searched manually by finding a spot that can elicit the largest response in the tibialis anterior with the lowest intensity. The location of the hotspot will be stored in the brain navigation system (Neuronavigation, Soterix Medical Inc.) to ensure a consistent stimulation location above the motor cortex at each time point [59]. Then, the resting motor threshold will be determined as the intensity of magnetic stimulation required to evoke MEPs with a peak-to-peak amplitude of 50 micro-V in at least 5 out of 10 consecutive trials. MEPs will subsequently be recorded at five stimulation intensities corresponding to 100%, 110%, 120%, 130%, and 140% of the session-specific RMT, with three trials collected at each intensity to characterize the stimulus–response relationship. To obtain a stable estimate of corticospinal excitability, an additional ten MEPs will be recorded at 120% RMT. To normalize MEP amplitudes, we will measure the maximal motor wave (M-max) in soleus and tibialis anterior after TMS testing. Soleus and tibialis anterior M-max will be measured by applying maximal single square pulses to the tibial nerve in the popliteal fossa and the common peroneal nerve around the head of the fibula, respectively.

Spinal motor evoked potentials (SMEPs) will be assessed with double-pulse stimulation (Digitimer, Model DS7A, Welwyn Garden City, UK) delivered over L1-L2 (two monophasic pulses with 1ms pulse width and a 50 ms inter-stimulus interval). Surface EMG will be recorded from the more affected side or dominant side in case of symmetrical involvement from four lower-limb muscles: soleus, tibialis anterior, rectus femoris, and biceps femoris. The same amplifier will be used to both amplify and band-pass-filter the data, as described above. Recruitment curves will be generated by increasing stimulation intensity from 5 mA to the participant’s maximal tolerable level in 5-mA increments. At each intensity, five paired-pulse stimulations were delivered with 5-second inter-trial intervals.

### 2.5. Assessment timeline

As outlined in Table 1, feasibility and safety outcomes will be measured throughout the study. Acceptability outcomes will be measured post-training immediately. Clinical outcomes will be measured at three time points: (1) baseline, (2) immediately post-training (two or three days after completing the 12 sessions), and (3) eight-week post-training. There will be two visits at each time point: one for clinical and mobility assessments, and the other for neurophysiological testing and an interview. Safety outcomes will be measured throughout the study.

### 2.6. Data management & analysis

Study data will be entered into a secure, password-protected electronic database by the University Health Network. Participants will be assigned a unique study identification number, and identifying information will be stored separately from research data. Electronic data will be stored on the secure institutional server, and paper records will be stored in locked cabinets in the secured research office. Feasibility outcomes (recruitment, retention, adherence, completion rates) will be summarized descriptively using means, standard deviations, frequencies, and percentages. Regarding TAM-2, items will be grouped into predetermined domains, and scores within each domain will be averaged to generate domain-specific scores. Conventional content analysis will be used to analyze the interview transcripts, given the exploratory nature of the study and limited research in this area. Interviews will be recorded, transcribed, and analyzed inductively by two members of the research team. The researchers will independently review the same transcripts, then meet to identify codes and create a preliminary codebook. This process will be repeated until a final codebook is created, and then the final codebook will be applied to the transcripts. Next, the research team will meet to review the codebook and group the codes, which will then be organized into categories and themes [24,39,61]. Adverse events will be reported descriptively by frequency and type.

All statistical analyses will be performed using SPSS (IBM SPSS, Chicago, USA) for the available data. A two-way repeated-measures ANOVA (group × time) will be conducted to analyze changes in clinical and neurophysiological outcomes across three study groups and time. The effect sizes with 95% confidence intervals will be reported, and the proportion of missing data (if applicable) will be described to inform the design and sample size calculation of a future fully powered trial.

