**Conclusion:**

Findings will help to determine whether neuromodulation-augmented balance training is feasible, safe, and acceptable for PwMS and will guide the design of a future fully powered RCT.

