Our team has developed a balance training platform that integrates visual feedback balance training (VFBT) with closed-loop FES for ankle muscles [24,37,38]. We have tested the feasibility and preliminary efficacy of this protocol in individuals with incomplete SCI who had difficulty in balance but were still able to stand without support [24,39]. However, for individuals with lower levels of function, particularly those with knee and hip impairments, FES for the ankle muscles may be insufficient to provide the postural support necessary for effective balance training [27,40,41]. Although proximal muscles could be stimulated by additional FES channels, this would significantly increase the system’s complexity. Rather, TSS offers a more effective way to concurrently modulate excitability across several spinal segments [28–30,36], and to augment multi-muscle activation without adding technical burden. This synergistic interaction is supported by preliminary results from our research group in people with incomplete SCI, showing greater functional benefits when TSS is administered concurrently with closed-loop FES (TSS + FES) during balance tasks [42,43].

Given the novelty of this combined neuromodulation approach and the lack of feasibility data in PwMS, a pilot randomized controlled trial (RCT) is warranted before designing a fully powered RCT. Therefore, the main purpose of this study is to assess the feasibility, acceptability, safety, and adherence of neuromodulation-augmented balance training interventions in PwMS. The second purpose is to investigate the preliminary clinical efficacy on balance performance, mobility, balance confidence, fear of falling and neural excitability. We hypothesize that the intervention will be feasible and acceptable with minimal adverse events, and that the combined neuromodulation group (TSS + FES) will show greater functional and neurophysiological improvements than FES-only or sham stimulation groups.

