## 2. Methods & materials

### 2.1. Participants & eligibility criteria

This multi-method study includes a pilot RCT to evaluate feasibility, acceptability, safety and preliminary efficacy of this novel neuromodulation-augmented balance training program and a qualitative descriptive study to capture patients’ experiences and perspectives [44]. This study will take place at the Lyndhurst Centre, a tertiary rehabilitation hospital, and has been approved by the University Health Network Research Ethics Board (Approval #25–5549, Version 5, December 29, 2025) and is registered at ClinicalTrials.gov (Identifier: NCT07174973). A formal sample size calculation is not required, as this is a pilot RCT [45]. We plan to recruit 24 participants (eight in each group), based on our previous studies in people with SCI using non-invasive neuromodulation.

For recruitment, we will use multiple strategies, including clinicians’ referrals, posting flyers at outpatient MS clinics, community MS programs, and existing research registries/databases (MS Canada). Participants will be allowed to continue their usual medical care throughout the study period. Written informed consent will be obtained from all eligible participants prior to baseline assessment. Given the small sample size, single-site design, and low-risk nature of the interventions, a formal independent data monitoring committee will not be required for this pilot RCT. Participant safety and study conduct will be monitored by the principal investigator, and any adverse events will be reported to the University Health Network Research Ethics Board. In addition, ongoing monitoring will occur through regular research team meetings to review recruitment progress, protocol adherence, intervention fidelity, data completeness, and adverse events.

Fig 1 shows the SPIRIT Timeline for the study, Table 1 summarizes the inclusion and exclusion criteria, and Table 2 shows the template for Intervention Description and Replication (TIDieR) checklist.

**Table 1 pone.0346491.t001:** Inclusion and exclusion criteria.

Criteria	
Inclusion	Confirmed diagnosis of MS based on the revised McDonald criteria Age 18–65 years Ability to walk at least 100 meters with or without an assistive device Self-reported balance difficulties during daily activities

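### Feasibility and safety are the trial's main purpose but are summarised by point figures only; 95% confidence intervals are planned only for the exploratory effect sizes

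*Protocol article*

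**What the plan says.** The Introduction states that "the main purpose of this study is to assess the feasibility, acceptability, safety, and adherence of neuromodulation-augmented balance training interventions in PwMS", and adds the hypothesis: "We hypothesize that the intervention will be feasible and acceptable with minimal adverse events". The Abstract's conclusion says: "Findings will help to determine whether neuromodulation-augmented balance training is feasible, safe, and acceptable for PwMS". Section 2.4.4 labels the efficacy outcomes as exploratory.

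Section 2.6 then names the statistics for each set of outcomes:

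- Feasibility: "Feasibility outcomes (recruitment, retention, adherence, completion rates) will be summarized descriptively using means, standard deviations, frequencies, and percentages".
- Safety: "Adverse events will be reported descriptively by frequency and type".
- Clinical and neurophysiological outcomes: a group-by-time repeated-measures ANOVA, followed by "The effect sizes with 95% confidence intervals will be reported".

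On size, section 2.1 says: "We plan to recruit 24 participants (eight in each group), based on our previous studies in people with SCI using non-invasive neuromodulation". It gives no formal calculation and no precision target. Section 2.4.1 defines retention as a proportion of participants, adherence as sessions completed out of 12, and recruitment relative to the number screened.

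**The concern.** Uncertainty is to be quantified for the secondary aim and not for the main one. This is more than silence: section 2.6 lists the summaries for the main outcomes and places the intervals elsewhere.

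The pilot is meant to inform a fully powered trial, and its feasibility results are to appear in their own publication (section 2.7). In groups this small, a high retention figure or the absence of a reaction looks more reassuring than it is. The text gives no numeric feasibility or safety criterion, so a reader of the results would have neither a threshold nor a measure of precision. The combined TSS + FES programme is the newest element and has the fewest participants.

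**Working it through.** **Inputs from the protocol.** Three groups of eight: 3 × 8 = 24. Groups 2 and 3 receive active FES: 2 × 8 = 16. Only group 3 receives active TSS: 8. The document states no target rate or precision, so there is no further figure to reproduce.

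**Assumed inputs.** The observed counts below are illustrations; the protocol predicts none.

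**Formula.** For x out of n, the exact (Clopper-Pearson) 95% limits are the 2.5% quantile of Beta(x, n − x + 1) and the 97.5% quantile of Beta(x + 1, n − x). For x = 0 the two-sided upper limit reduces to 1 − 0.025^(1/n). The one-sided 95% upper bound is 1 − 0.05^(1/n). The chance of seeing no affected participant when the true risk is p is (1 − p)^n.

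**No participant with a given reaction:**

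| Exposure | n | Two-sided upper limit | One-sided upper bound | Chance of seeing none if true risk is 10% |
|---|---|---|---|---|
| All participants | 24 | 1 − 0.025^(1/24) = 14.2% | 1 − 0.05^(1/24) = 11.7% | 0.9^24 = 8% |
| Active FES | 16 | 1 − 0.025^(1/16) = 20.6% | 1 − 0.05^(1/16) = 17.1% | 0.9^16 = 19% |
| Active TSS + FES | 8 | 1 − 0.025^(1/8) = 36.9% | 1 − 0.05^(1/8) = 31.2% | 0.9^8 = 43% |

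**Retention:**

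- 24/24 = 100%: 86% to 100%.
- 22/24 = 92%: 73% to 99%.
- 21/24 = 88%: 68% to 97%.
- If also shown for the eight on TSS + FES: 8/8 gives 63% to 100%, and 7/8 = 88% gives 47% to 99.7%.

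**Recruitment.** The denominator is the number screened, which is not known in advance. If 24 enrolled out of 40 screened, 60% (43% to 75%); out of 80 screened, 30% (20% to 41%).

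Precision is therefore poorest for safety in the group of eight, and better for overall retention.

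**The case against.** The strongest reply is that this is an article-length protocol of a pilot. Whether a descriptive proportion carries an interval is often settled in an analysis plan or at reporting, and nothing in section 2.6 would have to be contradicted to add one. Feasibility and acceptability are also judged on more than rates: section 2.6 plans TAM-2 domain scores and a content analysis of interviews. This lowers the severity. It does not remove the point, because the section names the statistics for the main outcomes, leaves intervals out of that list, and names them for the effect sizes.

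Several stronger readings are tempting, and the document does not support them:

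- A reader might infer that the programme will be pronounced feasible or safe on these figures. No such rule is stated; the Abstract claims only that findings will contribute to that judgement. Without a threshold one cannot say that the figures are inadequate in general, and 24/24 retained would have a lower limit of 86%.
- A reader might infer that adverse events will be given as percentages. Section 2.6 says frequency and type only.
- A reader might infer that only 16 people are exposed to stimulation. Sixteen receive active FES during training, but group 1 has brief sensory-level stimulation in each session (2.3.1), and the neurophysiological tests in 2.4.6 are not restricted by group.
- A reader might infer that the mean and standard deviation will misdescribe adherence. That depends on data not yet seen, and the listed frequencies can already show the distribution of sessions.

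It is also fair to say that retention by group is not something the protocol plans, and that the one-sided bounds for zero events are lower than the two-sided ones. Both sets are shown above for that reason.

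**Conclusion.** The point holds in a limited form. The outcomes that carry the main purpose have no planned measure of precision, while the exploratory ones do, and at these numbers the missing intervals are wide enough to change how a result reads. With no affected participant, the risks that cannot be excluded reach 14%, 21% and 37% (two-sided) or about 12%, 17% and 31% (one-sided) for 24, 16 and 8 participants.

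These figures assume full recruitment of eight per group, complete follow-up for adverse events, and counting by participant. Fewer participants would widen them. Intervals would show the imprecision without reducing it, and would not replace a feasibility or safety criterion. Severity is minor to moderate: a matter of reporting and interpretation, with no error of calculation in the plan.

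**What to change.** In section 2.6:

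1. Report retention, and the number of participants (not events) with at least one adverse event of each type, with exact Clopper-Pearson 95% intervals. Give them for all 24, for the 16 on active FES and for the 8 on active TSS + FES.
2. Report recruitment with an exact interval on the number screened.
3. State the feasibility and safety conclusions together with these intervals, and say whether each limit is one-sided or two-sided. If no participant on TSS + FES has a given reaction, for example, say that a risk of up to 37% (two-sided) is not excluded.

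Showing the full distribution of sessions attended is an optional addition.

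The cost is a few sentences and minutes of analysis, and the reported figures will look slightly less favourable. Design, recruitment and participant care are unaffected.

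### The named repeated-measures ANOVA drops, outcome by outcome, anyone missing one of three time points, so it fits poorly with the stated available-data basis and costs precision

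*Protocol article*

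**What the plan says.** Section 2.6 of the protocol article sets the data basis and names the model in two adjoining sentences: "All statistical analyses will be performed using SPSS (IBM SPSS, Chicago, USA) for the available data. A two-way repeated-measures ANOVA (group × time"). In full, the second sentence reads: "A two-way repeated-measures ANOVA (group × time) will be conducted to analyze changes in clinical and neurophysiological outcomes across three study groups and time". No mixed model and no imputation is named for these outcomes. On missing values, the section says that "the proportion of missing data (if applicable) will be described", to inform the later trial.

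Section 2.5 gives the levels of the time factor: "Clinical outcomes will be measured at three time points: (1) baseline, (2) immediately post-training", and eight weeks after training. It also splits each time point into two visits, one for clinical and mobility tests and one for neurophysiology and the interview.

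Section 2.1 gives the size: "We plan to recruit 24 participants (eight in each group), based on our previous studies in people with SCI using non-invasive neuromodulation". The article accepts that follow-up may be incomplete, because section 2.4.1 makes it an outcome: "Retention is defined as the proportion of participants who completed all three assessment time points".

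**The concern.** A classical group-by-time repeated-measures ANOVA takes one row per participant and needs a value at every level of the time factor. In SPSS (GLM Repeated Measures), an incomplete row is deleted for that outcome. A participant who finishes training, is measured straight afterwards and then misses the 8-week assessment contributes nothing, not even to the post-training comparison. A reader who sees that the available data will be analysed would not expect observed values to be discarded in this way.

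What is at stake is the planning information. Section 2.6 wants effect sizes with confidence intervals for the next trial's sample size, and section 3 wants an effect size and a variance from this one. With eight per arm, each discarded participant matters. Under the named model these estimates would come from completers only.

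**Working it through.** **Inputs from the article.** Three groups of 8, and 3 × 8 = 24, which agrees with the stated total. There are three time points, so 24 × 3 = 72 planned values per outcome. No alpha, power, effect size, standard deviation or dropout rate is given (section 2.1: "A formal sample size calculation is not required, as this is a pilot RCT"), so there is no power figure to reproduce. All miss rates below are assumptions.

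**Step 1: does the method discard observed values?** A simulated 24 × 3 table was given three missing cells in three different participants. Keeping complete rows left 21 participants and 63 values. A mixed model on the long-format data used all 24 participants and 72 − 3 = 69 values. The six values lost were observed ones. SPSS itself was not run. The check rests on the complete-row requirement of the classical procedure.

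**Step 2: how many participants remain?** Assume baseline is complete and each follow-up is missed independently with probability m. Expected complete cases are 24 × (1 − m)². The chance that all 24 are complete is (1 − m)^48. Values used are 72 × (1 − m)², against 24 × [1 + 2(1 − m)] observed.

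| m | Complete cases | Per arm | Values used | Values observed |
|---|---|---|---|---|
| 5% | 21.7 | 7.2 | 65.0 | 69.6 |
| 10% | 19.4 | 6.5 | 58.3 | 67.2 |
| 15% | 17.3 | 5.8 | 52.0 | 64.8 |
| 20% | 15.4 | 5.1 | 46.1 | 62.4 |

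The chance of no incomplete participant is about 8.5% at m = 5% and 0.6% at m = 10%, so the problem is likely to arise even with good retention.

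**Step 3: the cost at post-training.** Suppose every loss is at 8 weeks only, so all 24 post-training values exist. For a between-arm contrast in change, with the variance pooled over three arms of n, the interval half-width relative to 8 per arm is

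sqrt(8/n) × t(0.975, 3n − 3) / t(0.975, 21).

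- n = 7: sqrt(8/7) = 1.069; 2.101/2.080 = 1.010; ratio 1.08.
- n = 6.4 (20% lost): 1.118 × 1.018 = 1.14.
- n = 6: 1.155 × 1.025 = 1.18.
- n = 5.6 (30% lost): 1.195 × 1.033 = 1.23.

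**Step 4: is bias the larger problem?** One assumed scenario was simulated 20,000 times: unit variance, correlation 0.6 between time points, and a true post-training difference of 0.5 SD between Groups 3 and 1. The 8-week visit was missed by 30% of those with no early gain and by 10% of the others. On average 19.5 participants were complete. The complete-case post-training contrast averaged 0.484 with standard error 0.495. The same contrast on all 24 averaged 0.501 with standard error 0.445. The standard error rises by 0.495/0.445 = 1.11, or 11%, while the estimate shifts by only 0.016 from 0.5. In this scenario the cost is mainly precision.

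**The case against.** The strongest reply is that the two sentences do not strictly contradict each other. The available-data phrase is undefined and can be read as no imputation: each outcome is analysed on what was collected. Deletion within each ANOVA is then consistent with it. That stands. The two sentences fit poorly, but the text does not prove an impossibility. SPSS is not the obstacle either, since the same package fits mixed models.

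A reader might also infer that one missed visit removes a participant from every analysis. The article does not support this. Section 2.5 separates the clinical from the neurophysiological visit, and deletion is per outcome, so missing the neurophysiology visit leaves the clinical outcomes intact.

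A reader might further infer that the results will be biased because discomfort from stimulation drives withdrawal in the active arms. Intensities do differ: sections 2.3.1 to 2.3.3 give Group 1 a brief sensory-level stimulus that falls to zero, and Groups 2 and 3 active stimulation. But Group 1 does receive some stimulation. Item 13 of Table 2 links discomfort and fatigue to changes in intensity, not to withdrawal, and no missingness mechanism is stated. Bias is therefore a possibility only.

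The half-width ratios are also a best case for the alternative, because they put every loss at 8 weeks. Someone who leaves before the post-training assessment adds no post-training value under either method. At 8 weeks itself, a mixed model gains only indirectly, through correlation with earlier values.

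Finally, section 2.4.4 labels the efficacy outcomes exploratory, the main aims are feasibility, acceptability, safety and adherence, and missingness will be reported. This limits the importance of the point but does not remove it. Nor does a separate analysis plan, because the article itself names the method.

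**Conclusion.** The point holds in a limited form and should be fixed. The one model named for clinical and neurophysiological outcomes will, in its classical form, drop from an outcome's analysis anyone without all three values, including observed post-training values. Given 8-week-only losses that leave 7, 6.4 or 6 per arm, the post-training 95% interval is about 8%, 14% or 18% wider than with all 24. These sizes rest on assumed attrition. With no missed assessments the cost is zero, and with earlier losses the recoverable part is smaller. The effect falls on the estimates meant to plan the definitive trial. Recruitment, retention, adherence and adverse-event summaries do not depend on this model.

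**What to change.** In section 2.6, replace the ANOVA with a linear mixed model for repeated measures (SPSS MIXED, group by time). Include every randomised participant with any post-baseline value, analysed as randomised, with small-sample degrees of freedom such as Satterthwaite or Kenward-Roger. Keep the complete-case ANOVA as a sensitivity analysis, labelled complete-case per outcome, and report the number analysed for each outcome and time point.

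The cost is a change of wording, a few lines of syntax in the same package and slightly more analysis work. The covariance structure must be simple enough to fit 24 participants. An unstructured matrix over the two follow-ups, with baseline as a covariate, has 3 parameters; over all three time points it has 6. The mixed model relies on data missing at random, which is weaker than the missing-completely-at-random condition generally needed by the complete-case analysis, but it is still an assumption to state. If the ANOVA is kept as the main analysis, the section should at least say that it is complete-case for each outcome. That removes the ambiguity but not the loss of precision. The choice is best made before outcome data are seen.
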